### Primary outcome and secondary outcomes of the trial

The primary outcome of this study is the number of ventilator-free days (VFD) and survival to day 28, defined as the number of calendar days of unassisted breathing, after both ICU admission and start of mechanical ventilation to day 28, if the period of unassisted breathing lasted at least 24 consecutive hours. Unassisted breathing is defined as being extubated, ventilating with or without facemask, nasal prong oxygen, room air or tracheostomy breathing, but always without continuous positive airway pressure or pressure support of intermittent mandatory ventilation assistance. Patients who die before 28 days or are mechanically ventilated longer than 28 days are assigned zero ventilator-free days.

Secondary outcomes include clinical endpoints and cost-effectiveness outcomes. Clinical endpoints include the following: ICU and hospital length of stay (LOS); ICU, hospital, and 90-day mortality; development of moderate or severe ARDS; ventilator-associated pneumonia (VAP); development of atelectasis and pneumothorax; incidence of obstruction of the endotracheal tube (wherefore endotracheal tube exchange is indispensable); cumulative dose and duration of sedatives, cumulative dose and duration of neuromuscular blocking agents, development of delirium and incidence of side effects of nebulization of acetylcysteine and/or salbutamol. In addition, related healthcare costs will be compared from a health systems perspective over the time horizon of the trial and include direct medical and indirect costs of days of mechanical ventilation, stay in the ICU and hospital, cumulative use of sedatives and neuromuscular blocking agents, tracheostomies and ventilator-associated pneumonia.

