### Sample size calculation

Randomized trials assessing the efficacy of preventive nebulization are absent, which hampered power calculations. Therefore, the sample size calculation, based on a non-inferiority design, is calculated using the mean duration of invasive ventilation and the associated coefficient of variation, respectively 5 and 0.7 (log-transformed data) days [52], with a noninferiority margin of 10 %. A maximum difference in clinical effectiveness of 10 % between the ‘nebulization on indication’ arm as compared to the ‘preventive nebulization’ arm will be tolerated to consider a strategy of ‘nebulization on indication’ not to be inferior, with regard to the primary endpoint ventilator free days. Using these assumptions associated with the study design, a one-sided type I error of 0.05 and 80 % power (type II error), yields a sample size of 950 patients, which includes a 5 % anticipated drop out.

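### One 10% margin is used on two scales: 950 patients were sized on duration of ventilation, but non-inferiority is to be judged on ventilator-free days, where 10% is a much looser limit

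*Protocol article*

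**What the plan says.** All in the Protocol article.

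- **Sample size calculation, the inputs.** The number of patients is "calculated using the mean duration of invasive ventilation and the associated coefficient of variation, respectively 5 and 0.7 (log-transformed data) days", "with a noninferiority margin of 10" per cent. The other inputs are "a one-sided type I error of 0.05" and 80% power. The result "yields a sample size of 950 patients, which includes a 5 % anticipated drop out".
- **Sample size calculation, the decision rule.** The next sentence tolerates a 10% loss of clinical effectiveness before nebulization on indication is considered "not to be inferior, with regard to the primary endpoint ventilator free days".
- **Primary outcome and secondary outcomes of the trial.** VFD are counted over 28 days. "Patients who die before 28 days or are mechanically ventilated longer than 28 days are assigned zero ventilator-free days".
- **Data analysis.** The main comparison is of VFD and survival to day 28. Superiority is tested only after non-inferiority is confirmed.

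The margin is given neither in days nor as a ratio. No expected VFD and no expected mortality is given.

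**The concern.** For a survivor, VFD are what remains of 28 days after ventilation time is taken off. When ventilation lasts about 5 days, VFD are about 23, so the same percentage is a far larger number of days on the VFD scale than on the duration scale. Scoring deaths as zero moves the VFD scale further from the one used for sizing, because a VFD difference can then come from ventilation time, from deaths, or from both.

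The non-inferiority conclusion is read against this threshold, and the superiority test is reached only through it. A reader who sees the 5-day planning mean beside a 10% margin will take it as about half a day of ventilation. The decision sentence, read as 10% of mean VFD, permits considerably more. Nor does the stated 80% power say which of the two thresholds it belongs to.

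**Working it through.** **1. Reproducing 950.** Inputs from the sample size section: mean 5, coefficient of variation 0.7, log scale, 10% margin, one-sided 0.05, 80% power, 5% dropout; 1:1 allocation from the enrollment section.

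- Log SD = √ln(1 + 0.7²) = √0.3988 = 0.6315.
- Margin as a ratio of 0.9: −ln 0.9 = 0.1054.
- n per arm = 2 × 0.3988 × (1.645 + 0.842)² / 0.1054² ≈ 444.2, rounded up to 445.
- Total 890; 890 / 0.95 = 937, within 2% of 950.
- 950 × 0.95 ≈ 902 evaluable, or 451 per arm, which gives 80.5% power.

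The other variants tried do not come close: ln 1.1 as margin gives 1144, 0.1 on the log scale 1040, a log SD of 0.7 gives 1150 or more, 0.5 day with SD 3.5 on the raw scale 1276, and one-sided 0.025 gives 1188 or more. The calculation behind 950 is therefore best explained as a 10% ratio margin on duration: 5 / 0.9 = 5.56 days, about half a day longer.

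**2. The same 10% on VFD, per survivor.** No mortality is needed.

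- 28 − 5 = 23 VFD, and 10% of 23 = 2.3 days.
- Ventilation may go from 5 to 7.3 days; 7.3 / 5 = 1.46, or +46%.
- This takes 5 as an arithmetic mean. If it is a geometric mean, as the log-transformed note may suggest, a lognormal model gives about +37%.

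**3. The same 10% on VFD, all patients.** The article states no mortality, so 15% to 35% at day 28 is an assumption. Duration is lognormal (arithmetic mean 5, log SD 0.6315), VFD = max(28 − duration, 0), deaths = 0, 451 per arm, SE = SD × √(2/451). Power assumes no true difference: Φ(margin / SE − 1.645).

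| Assumed mortality | Mean VFD | SD | SE | 10% margin (VFD) | Same margin as extra deaths | Power for it | Duration margin (×1/0.9) in VFD | Power for it |
|---|---|---|---|---|---|---|---|---|
| 15% | 19.6 | 8.8 | 0.59 | 1.96 | 8.5 points | 95% | 0.47 | 20% |
| 20% | 18.4 | 9.7 | 0.65 | 1.84 | 8.0 points | 89% | 0.44 | 17% |
| 25% | 17.3 | 10.4 | 0.69 | 1.73 | 7.5 points | 80% | 0.41 | 15% |
| 30% | 16.1 | 10.9 | 0.73 | 1.61 | 7.0 points | 72% | 0.39 | 13% |
| 35% | 15.0 | 11.3 | 0.75 | 1.50 | 6.5 points | 63% | 0.36 | 12% |

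Extra deaths are 10% of survivors, for example 0.10 × 75% = 7.5 points at 25% mortality. Longer ventilation and extra deaths are alternative ways to use up the whole margin, not joint effects. With 5 as a geometric mean, the duration margin is 0.56 to 0.43 VFD over the same range, so about 0.4 to 0.5 VFD describes both readings.

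**4. What could be observed and still pass.** At 25% mortality: 1.73 − 1.645 × 0.69 ≈ 0.6 VFD.

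**The case against.** **The loose reading is only one reading.** The decision sentence speaks of a 10% difference in effectiveness and does not say 10% of mean VFD. The only margin with numbers behind it is the tight one on duration. This stands, and it is why the point is a contradiction to be reconciled rather than a claim that the trial has adopted the loose margin. It does not remove the point: if the duration tolerance was meant, the 80% power does not carry over to the endpoint that is analysed.

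**A reader might infer that non-inferiority could be declared despite clear harm.** The documents do not support that. The 1.5 to 2.0 VFD are true differences at the edge of what is tolerated. If the true loss equalled the margin, non-inferiority would be declared about 5% of the time, and at 25% mortality an observed loss above about 0.6 VFD would fail. ICU, hospital and 90-day mortality are separate secondary outcomes, the survival distributions are also compared (with no margin stated), and a safety board reviews the data at 317 and 634 patients. Extra deaths would not show only through VFD.

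**A reader might infer that 950 is wrong, or that 0.5 VFD is the correct margin.** Neither follows. On the duration scale 950 is approximately recovered. At 25% mortality it also gives about 80% power for 10% of mean VFD. Half a VFD over all patients is not 10% of 5 ventilator days either: at 25% mortality it is 0.5 / 0.75 = 0.67 day per survivor.

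**Acceptable width is a clinical judgement, and an article condenses.** Both are true. The full protocol or analysis plan may give the margin in days. The point rests only on what this article states, which is one percentage attached to two variables.

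**Conclusion.** The point holds as a contradiction of scale. The sample size section derives 950 from 10% of ventilation time, about half a day, and then applies 10% to VFD. Per survivor that is 2.3 days (+46%, or about +37% if 5 is a geometric mean). Over all patients it is about 2.0 to 1.5 VFD at an assumed 15% to 35% mortality, used up alternatively by 8.5 to 6.5 points more deaths. The duration margin is worth only about 0.4 to 0.5 VFD.

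The per-survivor figure needs only the article's own numbers and the reading of 10% as relative to mean VFD. The all-patient figures also need the assumed mortality, a lognormal duration, and a comparison of mean VFD with 451 per arm. Whether either margin is clinically acceptable is not decided here.

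**What to change.** In the sample size section, state the margin once, before the data are seen, as an absolute number of VFD on the analysed endpoint. Give its equivalents in ventilation time and in deaths under a stated mortality assumption, and restate the power of 950 patients for it.

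- **If 10% of mean VFD is meant:** write it in days (about 1.7 at 25% mortality). Report power of about 95% to 63% across 15% to 35% mortality, 80% at 25%. Word the conclusion as no more than that many VFD lost.
- **If the duration tolerance is meant:** report its VFD equivalent and replace the 80% by the power it has on VFD, about 20% to 12% over the same range and 15% at 25% mortality.

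The cost is protocol or analysis plan wording. It also means a less favourable stated figure: an openly wider margin in the first case, low power in the second.

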### Interim analysis

Interim analyses regarding safety are performed by an independent Data Safety Monitoring Board (DSMB) when 317 and 634 patients, have been included and have completed follow-up for the primary outcome. These interim analyses are not related to the non-inferiority hypothesis.

### Data analysis

The main analysis will compare the number of ventilator-free days and survival to day 28 between the two randomized groups. If the non inferiority of nebulization on indication compared to preventive nebulization can be confirmed, the superiority of nebulization on indication compared to preventive nebulization for the primary endpoint will be tested.

In addition, we will analyze the non inferiority between the two treatment groups regarding their survival distributions. Considering that survival times are not normally distributed and because some survival times will be censored by mortality, the Cox proportional-hazards model will be used to analyze the data. Significance will be expressed by the standard log rank test.

The effect of preventive nebulization on the primary outcome will also be investigated in prespecified subgroups based on patient categories (namely, patients with pneumonia versus patients without pneumonia and surgical versus medical admissions), and will be adjusted for the type of nebulizer (jet nebulizer or vibrating mesh), humidification method (active or passive), and type of flow used for nebulization (continues with external source or breath synchronized with an inline flow from the ventilator).

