### Setting

The trial is performed in at least seven ICUs, one in a university-affiliated hospital (the Academic Medical Center, Amsterdam) and six in teaching hospitals (Rijnstate Hospital, Arnhem; Onze Lieve Vrouwe Gasthuis, Amsterdam; Amphia Hospital, Breda, Oosterhout and Ettenleur; Antonius Hospital, Nieuwegein; Medical Center Haaglanden, The Hague and Leidschendam; and Isala Hospital, Zwolle) in the Netherlands.

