### Patient enrollment, randomization and blinding

Consecutive patients are screened for eligibility by local investigators and treating physicians. Patients meeting all inclusion criteria and no exclusion criteria are candidates for inclusion in the study and will be randomly assigned in a 1 to 1 ratio, after informed consent is given by the patient or their legal representative, to either a strategy of preventive nebulization of acetylcysteine and salbutamol four times daily (the ‘preventive nebulization’ arm) or nebulization of acetylcysteine or salbutamol on indication (the ‘nebulization on indication’ arm). Randomization will be performed by the local investigators and treating physicians as soon as possible, but always within 24 hours after start of invasive ventilation in the ICU. To avoid prediction of future patients’ allocation, randomization sequence is generated using a permuted block design with random block sizes stratified by study center. Maintenance of allocation concealment will be warranted using a central, dedicated, password-protected, SSL-encrypted web-based, automated randomization system, available 24 hours per day (ALEA® software, TenALEA consortium, Amsterdam, The Netherlands), developed by the Clinical Research Unit in the Academic Medical Center, Amsterdam, The Netherlands, which is not involved in the conduct of the study. Due to the nature of the intervention, blinding of the patients and caregivers is not possible. Outcomes assessment will be performed according to the study protocol by independent ICU physicians not involved in the trial. Investigators performing analysis are blinded for the intervention.

The assigned strategy is continued until tracheal extubation. If a patient requires reintubation and additional invasive ventilation within a period of 28 days, the strategy to which the patient is randomized will be resumed.

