### Clinical data to be collected

Data on baseline, demographic characteristics and disease severity are collected on the day of enrolment, including gender, age, height, weight, reason for ICU admission, reason for invasive mechanical ventilation and the APACHE II score. Furthermore, data are collected on the medical history including presence of diabetes mellitus, severe heart failure (New York Heart Association NYHA classification) [48], acute coronary syndrome or pulmonary disease, pulmonary or hematological malignancies, previous pulmonary radiation and/or surgery, and current use of immunosuppressive medication.

Data on clinical outcomes are collected on a daily basis up to day 28, discharge of the ICU or death, including data on duration of ventilation, length of stay in ICU and hospital. Location of the patient (ICU, hospital, other facility, or home) and life status (alive or deceased) is assessed on days 28 and 90.

Clinical data are collected on a daily basis up to day 28, discharge from the ICU or death, and these data include: intubation status (if extubated: time of extubation), tracheostomy status, mechanical ventilation parameters (see below), development of pulmonary complications (moderate or severe ARDS, pneumonia, atelectasis and pneumothorax); cumulative use and duration of sedatives and neuromuscular blocking agents; sedation score using the Richmond Agitation Sedation Scale (RASS) [35, 36]; level of pain (Numeric Rating Scale or Visual Analog Scale or Critical Care Pain Observation Tool or Behavioral Pain Scale) [37–39]; delirium score with the Confusion Assessment Method for ICU (CAM-ICU) or Intensive Care Delirium Checklist Screening (ICDCS) [40] score; amount and type of infused blood products; cumulative fluid balance and Sequential Organ Failure Assessment (SOFA) [49].

Parameters of mechanical ventilation are collected 1 hour after intubation and every day at a fixed time point up until extubation, day 28 or death including the following: tidal volume, respiratory rate, levels of PEEP, Ppeak and/or Pplateau, the level of pressure support, inspiration to expiration ratio, oxygen fraction of inspired air, minute volume and pulmonary compliance. The Lung Injury Score [50] and Oxygenation Index [51] are calculated.

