### General statistical considerations

Initial analyses will be performed according to the intention-to-treat (ITT) method. In addition, per-protocol (PP) analysis, including only those patients who complete the treatment according to the originally allocated protocol, will be done to check for the robustness of the results.

Continuous normally distributed variables will be expressed by their mean and standard deviation, or when not normally distributed as medians and their interquartile ranges. Categorical variables will be expressed as counts (n) and percentages (%). To analyze differences in continuous variables between the two groups, Student’s t-test will be used, or in case continuous data is not normally distributed, the Mann–Whitney U test will be used. Categorical variables will be compared with the Chi-square test or Fisher's exact tests. Statistical significance is considered to be at a *P* value <0.05 with one or two side test, depending on assessment of either non inferiority or superiority. The ICU mortality, hospital mortality, the length of ICU stay, and the length of hospital stay will be expressed with Kaplan-Meier curves.

When appropriate, statistical uncertainty will be expressed by 95 % confidence levels. All statistical analyses will be performed with the R language and environment for statistical computing [53].

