This trial also has some weaknesses: first, due to the nature of the intervention, blinding of patients and caregivers is not possible. Acetylcysteine has a very typical odor that cannot be mimicked, and consequently, nebulization with saline as placebo is not possible. Investigators who perform the analyses however are blinded for the intervention. In addition, the weaning process that directly, influences the primary outcome, as well as the airway care, will be performed by the attending ICU physician and nurse not involved in this study. Second, despite the fact that indications for nebulization of mucolytic agents or bronchodilating drugs in the ‘the preventive nebulization arm’ are set in the study protocol, indications are known to be highly interpretable. Third, as this is a multicenter study, differences in standard practice between participating centers exist. The study protocol, however, stresses that standard care be performed according to internationally accepted guidelines. Moreover, the randomization to both study arms is stratified per center.

Participating centers are allowed to administer humidification according to their local standard practice. Nebulization of mucolytic agents and bronchodilating drugs will be applied using either a jet nebulizer, the most commonly used type of nebulizer [13] or a vibrating mesh nebulizer. The type of nebulizer, as well as the type of humidification, are suggested to influence the fraction of nebulized medication reaching the lung [55, 56]. As a consequence, uniformity of the studied intervention might be diminished. This choice was made since we aim to study current nebulization practice and intent to avoid additional risks by introducing a new procedure with potential serious adverse outcomes. To control for these factors, randomization is stratified per center. In addition, data on applied care and on the use of relevant concomitant strategies possibly influencing outcomes are collected. Also, prespecified subgroup analyses are performed.

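### Randomization is stratified by center, but the tests named for the outcome comparison use neither center nor APACHE II: a valid analysis that gives up some precision

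*Protocol article*

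**What the plan says.** **Design.** Under Patient enrollment, randomization and blinding, the article states that the "randomization sequence is generated using a permuted block design with random block sizes stratified by study center". Under Setting, "The trial is performed in at least seven ICUs". The Discussion, after noting that nebulizer type and humidification vary with local practice, adds: "To control for these factors, randomization is stratified per center".

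**Primary analysis.** Under Data analysis: "The main analysis will compare the number of ventilator-free days and survival to day 28 between the two randomized groups". No covariate or stratum is named there. General statistical considerations gives Student's t-test for continuous variables and adds that "in case continuous data is not normally distributed, the Mann–Whitney U test will be used". No other test for ventilator-free days appears.

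**Survival analysis.** A Cox model with a standard log-rank test, with no strata mentioned.

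**Adjustment.** One sentence in Data analysis covers subgroups by pneumonia and by surgical or medical admission. It says that the effect on the primary outcome will be examined in them "and will be adjusted for the type of nebulizer (jet nebulizer or vibrating mesh), humidification method (active or passive"), with type of flow as a third factor. Center is not among the factors.

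**Baseline severity.** Clinical data to be collected lists, for the day of enrolment, "reason for ICU admission, reason for invasive mechanical ventilation and the APACHE II score". The score is used in no analysis described.

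**The concern.** Stratified randomization balances center between the arms, so between-center differences largely drop out of the true sampling variance of the treatment contrast. A two-sample t-test or Mann-Whitney test does not know this. Its standard error still includes the between-center variation, so the interval is wider than the design warrants. The protocol itself expects centers to differ in nebulizer, humidification, suction system and local guidelines. A baseline severity score is also recorded and left unused, although every death before day 28 counts as zero ventilator-free days, which makes severity a plausible predictor of the endpoint.

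In a non-inferiority trial planned at 80% power, an interval that is wider than necessary can be the reason for an inconclusive result. The stratification delivers balance on center; it delivers precision only if the analysis also uses center.

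**Working it through.** **1. Inputs (Sample size calculation).** Coefficient of variation 0.7 for duration of ventilation (log-transformed data), margin 10%, one-sided alpha 0.05, power 80%, 950 patients including 5% dropout. Allocation is 1:1.

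**2. Reproducing the planned size.**
- Log-scale SD = √ln(1 + 0.7²) = 0.6315. Margin = −ln(0.9) = 0.1054.
- n per arm = 2 × (1.645 + 0.842)² × 0.6315² / 0.1054², which gives 445, or 890 in total.
- With 5% dropout: 890 / 0.95 = 937, within 1.4% of 950.

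So the stated size follows from an unadjusted two-group calculation, and the design takes no credit for any covariate.

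**3. Power without adjustment.** 950 × 0.95 / 2 gives about 451 evaluable patients per arm. Power = Φ(0.1054 / (0.6315 × √(2/451)) − 1.645) = Φ(2.505 − 1.645) = 80.5%.

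**4. Power with adjustment.** If the covariates explain a share R² of the outcome variance, the residual SD becomes 0.6315 × √(1 − R²), and power = Φ(2.505 / √(1 − R²) − 1.645). The documents give no R², so a range is assumed:

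| Assumed R² | Total N for 80% power, incl. 5% dropout | Power with 451 per arm |
|---|---|---|
| 0 | 937 | 80.5% |
| 0.01 | 927 | 80.9% |
| 0.02 | 918 | 81.2% |
| 0.05 | 889 | 82.3% |
| 0.10 | 843 | 84.0% |
| 0.20 | 750 | 87.6% |

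**5. Size of the unadjusted test.** If center alone explains R² and is left out of the test, the actual one-sided size is 1 − Φ(1.645 / √(1 − R²)). This is 4.8% at R² = 0.02, 4.6% at 0.05 and 4.2% at 0.10.

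**6. What center alone adds.** After stratified randomization, the unadjusted test has power Φ((2.505 − 1.645) / √(1 − R²)): 80.8% at R² = 0.02 and 81.8% at 0.10. With center in the model the figures are 81.2% and 84.0%. The gain is about 0.4 to 2.2 points against the unadjusted test as it would actually run, or 0.7 to 3.5 points against the nominal 80.5%.

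**7. Limit of the calculation.** It uses log duration of ventilation, as the protocol's own sample size does. The endpoint is ventilator-free days, bounded and with zeros for death, so the gains are indicative.

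**The case against.** **The detail may sit in an analysis plan that is not shown.** Model covariates often do, and mere silence would be no finding. Here the article is not silent: it names its tests and names some adjustment factors, but omits the stratification variable. Still, the tests stand in a general section, and applying them to the primary endpoint is an inference. That reservation stands.

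**Some adjustment is planned.** Nebulizer type and humidification depend largely on the center, so adjusting for them would absorb part of the between-center variation. But the factors are named in the subgroup sentence, it is unclear whether they reach the main comparison, and they replace neither center nor baseline severity.

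**A reader might infer that the Discussion is contradicted.** It is not. Stratification does control local practice in the sense of balance between the arms, and the Discussion claims nothing about standard errors.

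**A reader might infer that the analysis is invalid or the trial underpowered.** The documents do not support this. The error is on the conservative side, so false non-inferiority does not become more likely, and about 80.5% power is reached under the protocol's own assumptions without any adjustment.

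**A reader might expect a larger gain.** With center at 2 to 10% of the variance and APACHE II at 10 to 20% of the remainder, the residual variance factor is 0.98 × 0.90 = 0.88 to 0.90 × 0.80 = 0.72, and a nominal 80% power becomes about 84 to 90%. That arithmetic is right, but most of the gain comes from APACHE II, and the documents say nothing on how strongly the score predicts ventilator-free days.

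**Conclusion.** The point holds as a loss of efficiency and a mismatch between design and analysis. The named tests ignore the randomization stratum and a recorded baseline score. The consequence is a slightly conservative test (one-sided size about 4.2 to 4.8% if center explains an assumed 2 to 10% of the variance) and forgone power: about 81 to 88% instead of about 80.5% if center and APACHE II together explain an assumed 1 to 20%. At the bottom of that range the gain is under half a point. All these figures rest on an assumed R² and on normal-theory variance for log duration. The unadjusted comparison remains valid, and nothing here calls the sample size into question.

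**What to change.** State before unblinding that:

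- The primary non-inferiority comparison includes center, as fixed effects or strata for all participating ICUs (the number may exceed seven), and baseline APACHE II, with robust standard errors.
- The adjusted effect and its confidence interval are reported on the same scale as the 10% relative margin. One option is a log-link model for mean ventilator-free days, which accommodates zeros and yields a ratio of means. If the margin is read as a 10% relative loss of ventilator-free days, the lower one-sided 95% bound of the ratio (on indication over preventive) is compared with 0.90. A difference in days cannot be read against the margin as it is now given.
- The APACHE II value used reflects data from before randomization, and a rule for missing scores keeps every randomized patient in the analysis.
- The Cox and log-rank analyses are stratified by center.
- The unadjusted comparison is kept as a sensitivity analysis.
- The sentence on nebulizer, humidification and flow says whether it applies to the subgroup analyses only or also to the main comparison.

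The cost is wording. Center is known from randomization and APACHE II is already collected, so no extra patients, visits or case record form fields are needed.

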## Methods/Design

### Design

This randomized controlled trial investigating the (cost-) effectiveness and safety of preventive nebulization of mucolytic agents and bronchodilating drugs in intubated and ventilated ICU patients, called the NEBULAE trial, is an investigator-initiated, national, multicenter, randomized controlled, open-label, two-armed non-inferiority trial in invasively ventilated patients admitted to participating ICUs in the Netherlands.

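### The supporting non-inferiority analysis relies on a log-rank test, which has no margin, and censors deaths without naming the event

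*Protocol article*

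**What the plan says.** The Data analysis section of the Protocol article makes ventilator-free days and survival to day 28 the main comparison. It then adds a further analysis: "we will analyze the non inferiority between the two treatment groups regarding their survival distributions". The method follows: "because some survival times will be censored by mortality, the Cox proportional-hazards model will be used to analyze the data". The criterion is: "Significance will be expressed by the standard log rank test". The section does not name the event in the Cox model and gives no margin on the hazard-ratio scale.

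The only margin is the 10% in Sample size calculation. It is attached to ventilator-free days, at "a one-sided type I error of 0.05". Under Primary outcome and secondary outcomes of the trial, a patient who dies before day 28 is given zero ventilator-free days.

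General statistical considerations adds: "The ICU mortality, hospital mortality, the length of ICU stay, and the length of hospital stay will be expressed with Kaplan-Meier curves". It does not say how death or discharge enters those curves. The same section summarises categorical variables as counts and percentages, compared by chi-square or Fisher's exact test. It makes the test one- or two-sided according to whether non-inferiority or superiority is assessed, and gives 95% confidence limits where appropriate.

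**The concern.** Two faults lie in the supporting analysis and a smaller one in the curves.

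- **No margin.** A log-rank test compares two event-time distributions against the hypothesis that they are equal. A significant result in favour of nebulization on indication would show superiority, which is more than is asked. A non-significant result shows nothing about non-inferiority, and a significant result the other way could still lie inside a tolerable margin. The question that the section poses needs a margin.
- **Deaths as censored times.** The primary endpoint treats death as the worst result. The supporting analysis removes the dead from the risk set. The two non-inferiority analyses therefore handle death in opposite ways, and the second can reassure when one arm has more deaths.
- **Kaplan-Meier curves.** Live discharge ends the risk of dying in the unit, and death ends the chance of live discharge. If either is handled as ordinary censoring, the curve for the other is too high.

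The trial is a "randomized controlled, open-label, two-armed non-inferiority trial" that could support giving up routine nebulization. A supporting analysis that can hide excess deaths in the on-indication arm errs in the unsafe direction.

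**Working it through.** **1. The plan's own figure.** From Sample size calculation: coefficient of variation 0.7, margin 10%, one-sided 0.05, 80% power, 5% dropout. Taking SD = √ln(1 + 0.7²) = 0.6315 and margin −ln(0.9) = 0.1054 on the log scale, n per arm = 2(1.645 + 0.842)² × 0.6315² / 0.1054², which gives 445. The total is 890, and 890/0.95 = 937, within 3% of the stated 950. Nothing in this calculation uses the Cox, log-rank or Kaplan-Meier analyses. The protocol gives no figure for them, so every rate in steps 3 to 6 is an assumption.

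**2. The censoring rule under each reading.**
- Event = death: a death is an event, so survival times cannot be censored by it.
- Event = liberation from ventilation (the likelier reading): censoring deaths gives a cause-specific hazard ratio. It compares liberation rates among patients still alive and ventilated. It does not compare the chance of coming off the ventilator alive.

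**3. How far the two can differ.** Let the liberation hazard be λ = 1/7 per day in both arms and the death hazard on the ventilator be δ. Liberated alive by day 28 = λ/(λ+δ) × (1 − exp(−28(λ+δ))).
- δ = 0.048: 0.7485 × 0.9952 = 74.5% liberated alive, with 25.0% dead before extubation.
- δ = 0.0686: 0.6756 × 0.9973 = 67.4% liberated alive, with 32.4% dead before extubation.

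The cause-specific hazard ratio for liberation is exactly 1.00, while 7.1 percentage points fewer patients come off the ventilator alive.

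**4. When the sicker patients both die more and wean later.** In a simulation, 40% of patients were sicker. Liberation hazards were 0.05 per day (sicker) and 0.20 (others), death hazards 0.06 and 0.005, and the death hazard was multiplied by 1.5 in one arm. In that arm the death-censored Cox hazard ratio for liberation was 1.04 (95% CI 1.01 to 1.07), which looks slightly favourable. The subdistribution hazard ratio was 0.92. Liberated alive fell from 75.6% to 71.7%, and mean ventilator-free days from 17.0 to 16.4.

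**5. The log-rank test as a criterion.** With 1:1 allocation and d events, power at hazard ratio 0.90 is Φ(√d/2 × 0.1054 − z). Suppose 60% to 80% of 902 to 950 patients are extubated, so d = 541 to 760.
- Two-sided 5% log-rank (z = 1.96): Φ(1.225 − 1.960) = 23% to Φ(1.452 − 1.960) = 31%. About 70% to 77% of trials would be non-significant although the liberation hazard is 10% lower.
- Non-inferiority against a hazard-ratio margin of 0.90 (my assumption; the plan sets none), with a true ratio of 1 and one-sided 0.05 (z = 1.645): power 34% to 42%. For 80% power, 4(1.645 + 0.842)²/0.1054² gives 2228 events, more than there are patients.

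**6. Kaplan-Meier if the competing event is censored.** With constant hazards, mean ICU stay L and final ICU mortality m, one minus Kaplan-Meier for death at day 28 is 1 − exp(−28m/L). The cumulative incidence is m(1 − exp(−28/L)).
- L = 8 days, m = 25%: 58% against 24%.
- L = 6 to 12 days, m = 15% to 30%: 30% to 75% against 14% to 30%.
- Live discharge at L = 8, m = 25%: 1 − exp(−28 × 0.75/8) = 93% against 0.75 × 0.970 = 73%.

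**The case against.** The main conclusion is protected. Ventilator-free days is the main analysis, it counts death against the arm where it occurs, and the Cox analysis is only an addition. That stands.

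Mortality is also a separate secondary outcome in the ICU, in hospital and at 90 days, and can be compared as counts and percentages. With 25% against 32% dead and 475 patients per arm, the expected z is 0.07/√(0.25×0.75/475 + 0.32×0.68/475) = 2.4. That stands in part: power at that z is Φ(2.4 − 1.96), about 67%, so the excess would often but not always be flagged.

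Four stronger readings are tempting, and the document does not support them.

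- A reader might infer that a death-censored Cox model is simply invalid. It validly estimates the cause-specific hazard ratio; in step 3, 1.00 is the right answer to that question. The fault is to let it stand alone for the outcome.
- A reader might infer that a non-significant log-rank result will be reported as non-inferiority. No section says so, and the plan's one-sided significance rule and confidence limits point the other way. What holds is that no hazard-ratio margin exists for a test or an interval to use.
- A reader might infer that the Kaplan-Meier curves will be biased. No censoring rule is given for them. Counting death as the end of stay, or following discharged patients for vital status (assessed on days 28 and 90), would avoid the bias.
- A reader might infer that the reported ICU mortality would be 58% instead of 24%. Mortality is a categorical outcome and would be given as a count and percentage; only the curve is at risk.

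An article may leave censoring details to an analysis plan. That excuses the silence on the curves. It does not excuse the log-rank criterion or the statement that mortality censors, both of which the article fixes.

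**Conclusion.** The supporting non-inferiority analysis is wrong as written. That a log-rank test has no margin, and that the censoring rule runs against the primary endpoint's handling of death, follow from the text and need no assumed rates. The sizes do rest on assumptions: a hazard ratio of 1.00 beside a fall from 74.5% to 67.4% liberated alive depends on constant hazards that I chose, and the simulated 1.04 on an assumed case mix. The point about the Kaplan-Meier curves is conditional on the competing event being censored.

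The consequence is limited to supporting and descriptive results. A reader might infer that the trial's main result or its size is in doubt; neither is. The ventilator-free-day comparison and the 950 patients do not depend on these analyses. This is a correction worth making before analysis, not a flaw that undermines the trial.

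**What to change.** 1. Name the event: liberation from ventilation alive, using the primary outcome's own definition of unassisted breathing.
2. Treat death as a competing event. Report the cumulative incidence of liberation alive by arm, together with cause-specific hazard ratios for liberation and for death.
3. Replace the log-rank p-value by a confidence limit at the trial's one-sided 0.05 level (the relevant limit of a two-sided 90% interval), set against a margin prespecified on the scale used. If no margin can be justified, or power is as low as step 5 suggests for a hazard-ratio margin of 0.90, drop the non-inferiority claim from this analysis and present it as descriptive.
4. In General statistical considerations, show ICU and hospital death and live discharge as cumulative incidence curves. Keep Kaplan-Meier for all-cause mortality to day 90.

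The cost is wording in the protocol or analysis plan. Daily intubation status, extubation time, and vital status on days 28 and 90 are already collected (Clinical data to be collected), and the methods are standard in R. No new data or patients are needed.
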